### Statistical Analysis Plan

For the analysis plan, 6 cascade bars, as explained in Tables 2 and 3, will be used to generate the cascades of care for T2D and HT, respectively. A fixed denominator approach will be followed as it enables readers to see the leakages between stages of the continuum of care [39]. The denominator is the total number of eligible individuals aged 40 and above having T2D (for the T2D cascade of care) and HT (for the HT cascade of care). We will produce the cascade of care for T2D and HT for the selected ODs hosting different existing care models. These cascades of care—in essence, a series of bar charts—will subsequently be translated into cumulative probabilities. The bivariate analysis will be used to identify potential factors associated with the outcome variables—prevalence, testing, diagnosis, in care, in treatment, and under control bars. At the initial stage, the chi-square test will be used to determine the association between explanatory variables and outcome variables. The explanatory variables will include participants’ age, sex, marital status, educational level, household wealth quintile, health care utilization, and care model setting. Variables with statistically significant level (*P*<.2) will be included in a multiple logistic regression model. In addition to the aforementioned variables, BMI, lifestyle, knowledge of T2D and HT, self-management, and social support will be included in the multiple logistic regression model for the outcome variables—in care, in treatment, and under control bars [24,25]. In the multiple logistic regression model, the backward elimination method will be used. The process will start with all the identified explanatory variables. Then, variables with the highest *P* value will be eliminated from the model one by one at a time. The process will be repeated until all the variables in the model are statistically significant with a cut-off point of *P* value <.05. This knowledge will allow us to identify which characteristics stimulate the probability of not reaching the next step in the cascade of care, thereby identifying patient groups not adequately reached.

**Table 2 table2:** Defined groups of participants for each bar of the cascade of care for T2D^a^.

Bars of the cascade of care for T2D	Definitions	Questions extracted for analysis

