1. Prevalence of the target population living with T2D	Participants having biochemical measurement of FBG^b^ (capillary plasma value) ≥126 mg/dl (7 mmol/L) and HbA_1c_^c^ level ≥6.5% [24,40,41]	Measurement of FBG Measurement of HbA_1c_
		Have you ever been told by a doctor or other health worker that you have T2D?
	or Participants reporting use of drugs for T2D, irrespective of their biomarker values	
2. Number of the target population with T2D ever tested for T2D	Classified patients with T2D having had FBG tested in the last 3 years	Have you ever had your blood glucose tested in the last 3 years?
3. Number of those tested ever diagnosed for T2D	Tested patients with T2D reporting ever being told by a doctor or other health worker as having T2D	Have you ever been told by a doctor or other health worker that you have T2D?
4. Number of those diagnosed in care	Diagnosed patients with T2D reporting getting treatment/care for their conditions at least once in the past 12 months	Did you get treatment/care for your T2D condition in the past 12 months?
5. Number of those in care receiving treatment	In-care patients with T2D reporting using drugs for T2D or insulin in the past 2 weeks or in-care patients with T2D reporting following advice to lose weight, stop smoking, do physical exercise, and be on special prescribed diet	Are you currently receiving any of the following treatment/advice for your T2D condition prescribed by a doctor or health care worker? Insulin or drugs (medication) that you have taken in the past 2 weeks Are you currently receiving any of the following treatment/advice for your T2D condition prescribed by a doctor or health care worker? Special prescribed diet and advice to lose weight and advice to stop smoking and advice to start or do more physical exercise
6. Number of those receiving treatment being under control	In-treatment patients with T2D having HbA_1c_ level <8% [24]	Measurement of HbA_1c_ for the known T2D

^a^T2D: type 2 diabetes.

^b^FBG: fasting blood glucose.

^c^HbA_1c_: glycated hemoglobin A_1c_.

**Table 3 table3:** Defined groups of participants for each bar of the cascade of care for HT^a^.

Bars of the cascade of care for HT	Definitions	Questions extracted for analysis
1. Prevalence of the target population living with HT	Participants having systolic blood pressure ≥140 mmHg or diastolic blood pressure ≥90 mmHg [12] or	Measurement of blood pressure (mean of the second and third readings)

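### On the only denominator stated, the models for diagnosis and later bars estimate passing every step so far, but the plan reads them as failure at the next step

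*Protocol article*

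**What the plan says.** All of this is in the Protocol article, Methods, Statistical Analysis Plan, with Tables 2 and 3.

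- Approach: "A fixed denominator approach will be followed as it enables readers to see the leakages between stages of the continuum of care".
- Denominator: "The denominator is the total number of eligible individuals aged 40 and above having T2D", with a parallel clause for HT. No other denominator is given.
- Scale: the cascades "will subsequently be translated into cumulative probabilities".
- Regression outcomes: "outcome variables—prevalence, testing, diagnosis, in care, in treatment, and under control bars". Chi-square screening and multiple logistic regression with backward elimination are applied to these.
- Nesting: each bar after the second is defined within the one before. For T2D, bar 3 is "Tested patients with T2D reporting ever being told by a doctor or other health worker as having T2D" and bar 4 is "Diagnosed patients with T2D reporting getting treatment/care for their conditions at least once in the past 12 months". Bars 5 and 6 are likewise restricted to those in care and those in treatment, and Table 3 repeats the pattern for HT.
- Inference: the models are to "identify which characteristics stimulate the probability of not reaching the next step in the cascade of care".

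**The concern.** The outcome and the conclusion are different quantities. A person with T2D counts in the in-care bar only if tested, diagnosed and in care. Over all cases, a logistic model for that bar therefore mixes three steps. A statement about who drops out at the next step needs the outcome among people who had reached the step before.

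The plan's purpose is to locate leaks, and care model is one of the explanatory variables. A characteristic, or a care model, that differs only in detection could be reported as associated with poor linkage, treatment or control. The reverse can also happen: a real difference at a later step could be offset in the model by an opposite difference earlier. The actions that follow would differ: case finding in one situation, retention or treatment quality in the other.

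**Working it through.** The plan gives no step probabilities and no odds ratios for the cascade, so there is no figure of its own to reproduce on this point. All step probabilities below are assumptions. From the article come the nesting (Tables 2 and 3), the 5072 participants (Results) and the 10% T2D prevalence (Sampling and Sample Size), which give 5072 × 0.10 ≈ 507 cases.

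**Formulas.** Let s_j be the probability of passing step j among those who reached step j−1. The bar over all cases is B_k = s_1 × … × s_k. The fixed-denominator odds ratio (OR) compares B_k/(1−B_k) between groups. The next-step OR compares s_k/(1−s_k).

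**1. Effect at diagnosis only.** The diagnosis bar is 70% v 50% of cases. The later steps are the same in both groups: 80% in care, 90% treated, 40% controlled.

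| Bar | Group 1 | Group 2 | OR over all cases | Next-step OR |
|---|---|---|---|---|
| In care | 0.70×0.80 = 0.560 | 0.50×0.80 = 0.400 | (0.560/0.440)/(0.400/0.600) = 1.91 | 1.00 |
| Treated | 0.560×0.90 = 0.504 | 0.400×0.90 = 0.360 | (0.504/0.496)/(0.360/0.640) = 1.81 | 1.00 |
| Controlled | 0.504×0.40 = 0.2016 | 0.360×0.40 = 0.144 | (0.2016/0.7984)/(0.144/0.856) = 1.50 | 1.00 |

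**2. Range over other assumptions.** Four sets of step probabilities were tried, from low to high coverage, each with a factor that lowers only diagnosis. The carried-over OR was 0.35–0.68 for in care, 0.41–0.69 for treated and 0.55–0.72 for controlled. The true step OR was 1.00 throughout.

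**3. How often it would be declared significant.** One of those sets was simulated: tested 0.7, diagnosed 0.8 v 0.6, in care 0.7, treated 0.8, controlled 0.5, with 507 cases split evenly, simple random sampling, unadjusted chi-square tests and 3000 surveys.

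| Share with P<.05 | In care | Treated | Controlled |
|---|---|---|---|
| Over all cases | 63% | 49% | 24% |
| Among those at the previous bar | 5% | 5% | 5% |

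The plan's design effect of 1.5 leaves about 169 effective cases per group (253/1.5). Normal-approximation power for the first row is then 48%, 37% and 18%.

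**4. Offsetting effects.** Suppose diagnosis among the tested is 0.8 v 0.6 and linkage to care is 0.6 v 0.8, with testing at 0.7. The in-care bars are 0.7×0.8×0.6 = 0.336 and 0.7×0.6×0.8 = 0.336, so the OR over all cases is 1.00. The next-step OR is (0.8/0.2)/(0.6/0.4) = 2.67.

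**5. What the chart would show.** Take steps of 90/80/60/90/40% in X and 60/80/85/90/45% in Y. The in-care bars are close (43.2% v 40.8%), but the diagnosis bars are 72% v 48%. Dividing adjacent bars gives 43.2/72 = 60% and 40.8/48 = 85%, an OR of (0.60/0.40)/(0.85/0.15) = 0.26. The in-care regression over all cases would give (0.432/0.568)/(0.408/0.592) = 1.10.

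**The case against.** The strongest reply is that the regression denominator is inferred. The denominator sentence is attached to the cascade, which the section describes as essentially bar charts, and no sentence names the analysis set of the logistic models. The prevalence outcome cannot be modelled among people who all have the disease, so the fixed denominator cannot govern every regression. The row labels in Tables 2 and 3 are worded step by step and could be read as conditional. This stands as a limit: a reader might infer that the plan rules out conditional models, and the text does not say that. It does not remove the problem. The outcomes are named as the bars, the only denominator given is all cases, and under the conditional reading the regression set would depart from that denominator without being stated.

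Second, under Study Design the knowledge items are directed at known patients in particular, and knowledge enters the last three models. If it is missing for undiagnosed people, complete-case fitting would restrict those models to diagnosed people and the diagnosis effect would not carry over. That is possible, but it would be an unannounced change of denominator, and the treatment and control models would still be cumulative from diagnosis onward.

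Third, the aims compare the cascades themselves, and adjacent bars reveal a step loss directly, as item 5 of the working shows. This stands. A reader might infer that care-model differences would be hidden altogether. They could be masked in the adjusted regressions, but not on the planned charts.

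Fourth, the same sentence ends by speaking of patient groups not adequately reached. That is a coverage question, which models over all cases answer validly. This stands too: the models are sound for coverage, and only the next-step interpretation is at fault.

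**Conclusion.** The stated outcome and the stated inference do not match. On the only denominator given, the diagnosis, in-care, in-treatment and under-control models estimate passing all steps up to that bar, so a next-step conclusion does not follow from them. The prevalence model runs over all participants. For testing, the first step among cases, the two quantities coincide. Neither is affected.

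The size is illustrative: carried-over ORs of 1.91, 1.81 and 1.50 against a true 1.00, and a true step OR of 2.67 reduced to 1.00 when effects oppose. It would be tempting to say that early losses will dominate every later model. The documents do not support that: they give no step probabilities, and in the diagnosis-only illustrations the carry-over weakens towards the last bar and often falls short of P<.05 there.

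**What to change.** Keep the fixed denominator for the charts and for models described as coverage among all people with the disease. Base any next-step statement on logistic models fitted among those who reached the previous bar: diagnosed among tested, in care among diagnosed, treated among in care, controlled among treated. Use the same three-stage weights, and state the analysis set of each regression. If these models are not wanted, reword the inference as failing to reach a given bar among all people with the disease.

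The article reports that data are collected and analysis is pending, so the cost is wording and one further set of models. The statistical price is smaller sets. Under the step probabilities simulated above, 507 cases would leave about 355 tested (507×0.70), 248 diagnosed (507×0.49), 174 in care (507×0.343) and 139 treated (507×0.2744), with wider intervals at the later steps. Those sets are also selected by the earlier steps, so their results should be reported beside the coverage models.

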	Participants reporting use of drugs for HT, irrespective of their blood pressure values	Have you ever been told by a doctor or other health worker that you have HT?
2. Number of the target population with HT ever tested for HT	Classified patients with HT having had a blood pressure measured in the last 3 years	Have you ever had your blood pressure measured in the last 3 years?
3. Number of those tested ever diagnosed for HT	Tested patients with HT reporting ever being told by a doctor or other health worker as having HT	Have you ever been told by a doctor or other health worker that you have HT?
4. Number of those diagnosed in care	Diagnosed patients with HT reporting getting treatment/care for their conditions at least once in the past 12 months	Did you get treatment/care for your HT condition in the past 12 months?
5. Number of those in care receiving treatment	In-care patients with HT reporting using drugs for HT in the past 2 weeks or	Are you currently receiving any of the following treatment/advice for your HT condition prescribed by a doctor or other health worker? Drugs (medication) that you have taken in the past 2 weeks
	In-care patients with HT reporting following advice to lose weight, stop smoking, do physical exercise, and reduce salt intake	Are you currently receiving any of the following treatment/advice for your HT condition prescribed by a doctor or other health worker? Advice to reduce salt intake and advice to lose weight and advice to stop smoking and advice to start or do more physical exercise
6. Number of those receiving treatment being under control	In-treatment patients with HT having systolic blood pressure <140 mmHg and diastolic blood pressure <90 mmHg [12]	Measurement of blood pressure (mean of the second and third readings) for the known HT

^a^HT: hypertension.

Because of the multistage stratified random cluster sampling, a 3-stage weighting procedure will be applied to account for (1) the fixed number of villages selected in each OD, (2) the fixed number of households selected in each village, and (3) the number of household members aged 40 and above in each selected household [25,30]. The statistic program Stata 14.2 (StataCorp) [42] will be used to perform the quantitative analyses.

Variables used to generate the cascade of care for T2D and HT are shown in Tables 2 and 3, respectively. The explanatory variables are detailed in Multimedia Appendix 6 [43-47].

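### Bar 2 of both cascades is labelled ever tested but defined as tested in the last 3 years, so earlier-diagnosed patients without a recent test drop out of bar 2 and every bar nested in it

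*Protocol article*

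**What the plan says.** The Statistical Analysis Plan section of the Protocol article builds six bars from Tables 2 and 3 on a fixed denominator: everyone aged 40 and over classified as having the disease (bar 1). The relevant T2D entries in Table 2 are:

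- Bar 1 admits, besides those who meet the biomarker criteria, "Participants reporting use of drugs for T2D, irrespective of their biomarker values".
- Bar 2, label: "Number of the target population with T2D ever tested for T2D".
- Bar 2, definition: "Classified patients with T2D having had FBG tested in the last 3 years".
- Bar 2, source question: "Have you ever had your blood glucose tested in the last 3 years".
- Bar 3: "Tested patients with T2D reporting ever being told by a doctor or other health worker as having T2D".
- Bar 4: "Diagnosed patients with T2D reporting getting treatment/care for their conditions at least once in the past 12 months".
- Bar 5, drug route: "In-care patients with T2D reporting using drugs for T2D or insulin in the past 2 weeks".
- Bar 6 is limited to treated patients and requires HbA1c below 8%.

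Table 3 repeats the structure for HT. Its bar 2 also carries an *ever tested* label, over the definition "Classified patients with HT having had a blood pressure measured in the last 3 years". Nothing in either table, or in the text around them, counts a patient who is already diagnosed or treated as tested.

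**The concern.** *Ever tested* and *tested in the last 3 years* are different groups, and the choice between them carries through the whole cascade, because each later bar is restricted to those who passed the one before. Bar 3 asks about diagnosis at any time, but only among people with a recent test. Someone with a long-standing diagnosis and no recent test therefore counts as having disease and as failing at the testing step.

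The cascade is meant to show at which step patients are lost. For such a patient the real gap, if there is one, is in monitoring or retention, yet it appears between bars 1 and 2. The patient is also coded as a failure in the logistic models for testing and diagnosis and, where the later conditions are met, for care, treatment and control. The third and fourth aims compare these cascades between care models, so a misplacement that varies between models would carry into the comparison.

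**Working it through.** The plan gives no figure for how many patients are affected, so there is nothing of its own to reproduce. The check has two parts.

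**1. Applying the definitions to one record.** The patient reports T2D drugs, has been told of T2D, had care in the past 12 months, took drugs in the past 2 weeks, has HbA1c 6.9%, and last had a glucose test more than 3 years ago.

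| Bar | Own condition met? | As written | If diagnosed counts as tested |
|---|---|---|---|
| 1 | yes | in | in |
| 2 | no (3-year window) | out | in |
| 3 | yes | out | in |
| 4 | yes | out | in |
| 5 | yes | out | in |
| 6 | yes | out | in |

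Now remove the care in the past 12 months. As written, the record is again out from bar 2 on. With the amended rule it is in at bars 2 and 3 and out from bar 4, where the loss belongs.

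**2. Size, under stated assumptions.** Let D be the true diagnosed share of bar 1, w the share of the diagnosed with no test in 3 years, and c the share of those untested patients who had care in the past 12 months. None of the three is in the documents.

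- Bar 3 as written = D × (1 − w). With D = 60%:
  - w = 2%: 0.60 × 0.98 = 58.8% (1.2 points lost)
  - w = 5%: 0.60 × 0.95 = 57.0% (3.0 points lost)
  - w = 10%: 0.60 × 0.90 = 54.0% (6.0 points lost)
- Bar 4 loses D × w × c. With D = 60% and w = 5%, that is 0, 1.5 or 3.0 points for c = 0, 0.5 or 1. Bars 5 and 6 cannot lose more points than bar 4.
- Bar 2 falls short of its *ever tested* label by at least D × w, taking a diagnosis to imply a test at some time. Undiagnosed people last tested more than 3 years ago add to the shortfall.

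For scale, the planned 5280 individuals at the 10% prevalence used for sample size give 528 T2D cases. With D = 60% and w = 5%, bar 3 loses 528 × 0.60 × 0.05 = 15.8 patients.

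**Between models.** If two models both had D = 60% but w were 2% in one and 10% in the other, bar 3 would show 58.8% against 54.0%. That is an apparent gap of 4.8 points with no true difference. It illustrates what could happen; it is not an estimate.

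**The case against.** The strongest reply is that the effect may be small and that several larger claims do not follow from the text. Most of this stands.

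- A reader might infer that bars 3 to 6 all fall by w in relative terms. That is exact for bar 3 only. For the later bars it would require recent testing to be unrelated to being in care. Patients in care are probably tested more often, so the loss there is probably smaller and could be nil.
- A reader might infer that any treated, controlled patient without a recent test is lost from bars 4 to 6 because of bar 2. Without care in the past 12 months, that patient fails bar 4 by its own rule.
- A reader might infer that T2D and HT are equally affected. The HT bar needs only one blood pressure reading in 3 years, which someone in HT care within the year would rarely lack.
- A reader might infer that the comparison of care models is biased. The documents give no testing frequency by model, so this is possible but not shown.
- A reader might infer that these patients are reported as never tested. The definition and question columns both state the window; only the label suggests it. Part of the problem is therefore labelling.

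What the reply does not remove is the nesting. A recent test is a condition for being counted as diagnosed, and no text rescues patients diagnosed earlier.

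**Conclusion.** The inconsistency is real and rests on the tables alone: label and definition of bar 2 disagree in both cascades, and later bars are not limited by their own conditions only. The direction is certain. Bar 2 is understated relative to its label, and no later bar can be overstated by this rule.

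The size is not known. Bar 3 falls by w in relative terms, or 1.2 to 6.0 points for the assumed D of 60% and w of 2% to 10%. Bars 4 to 6 fall by between 0 and at most the same number of points, probably less, and probably less for HT than for T2D. Bias between care models is conditional on w differing between them. The point should be settled before analysis, but its consequences should be stated as possible, not established.

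**What to change.** In both tables, define bar 2 as tested in the last 3 years, or ever told of the disease, or reporting drugs for it. Change the label to match, for example *tested in the last 3 years or previously diagnosed or treated*. The relabelling is needed as well as the new definition: an undiagnosed person last tested more than 3 years ago would still fall outside a bar called *ever tested*. State in the question column that bar 2 draws on all three items, so that label, definition and questions agree and each later bar is a true subset of the one before.

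Report the share tested in the last 3 years among the diagnosed as a separate monitoring indicator outside the cascade. It keeps the information in the 3-year item and shows w by care model.

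The cost is a recode of items already listed in Tables 2 and 3; the Results section says analysis was still pending. This assumes that the *ever told* and drug items were asked whatever the answer to the 3-year question, which should be confirmed against the questionnaire in Multimedia Appendix 2. One small downside remains: the amended bar 2 mixes recent testing with past diagnosis.

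### Bar 5 of both cascades admits drug-free patients only if all four lifestyle items are met, with no allowance for items that do not apply to the patient

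*Protocol article*

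**What the plan says.** The Statistical Analysis Plan section defines six bars per cascade on a fixed denominator, namely everyone aged 40 and over with the condition. Bar 5 has two routes joined by *or*.

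- **Drug route, T2D (Table 2):** "In-care patients with T2D reporting using drugs for T2D or insulin in the past 2 weeks or in-care patients with T2D" qualifying by the second route.
- **Lifestyle route, T2D, definition column:** "in-care patients with T2D reporting following advice to lose weight, stop smoking, do physical exercise, and be on special prescribed diet".
- **Lifestyle route, T2D, question column:** the stem is "Are you currently receiving any of the following treatment/advice for your T2D condition prescribed by a doctor or health care worker", and the items are "Special prescribed diet and advice to lose weight and advice to stop smoking and advice to start or do more physical exercise".
- **Lifestyle route, HT (Table 3), definition column:** "In-care patients with HT reporting following advice to lose weight, stop smoking, do physical exercise, and reduce salt intake".
- **Lifestyle route, HT, question column:** the same kind of stem, then "Advice to reduce salt intake and advice to lose weight and advice to stop smoking and advice to start or do more physical exercise".

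Bar 6 counts only patients already in bar 5. The same section adds covariates for the in-care, in-treatment and under-control outcomes: "BMI, lifestyle, knowledge of T2D and HT, self-management, and social support will be included in the multiple logistic regression model".

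**The concern.** Two of the four items, stopping smoking and losing weight, presuppose a condition that many patients do not have. A patient with nothing to stop and no weight to lose may never be given that advice. Under an all-four rule such a patient cannot be credited for the diet (or salt) and exercise care actually received.

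The plan chose a fixed denominator so that readers can see where patients are lost. A loss between bars 4 and 5 that the scoring rule itself creates would be read as a failure of the health system. Comparing care models is a stated aim, and the Introduction names lifestyle counselling as a service of the health center and peer educator models, so the lifestyle route is not incidental. The regression is meant to show which patient groups are not adequately reached; if smoking and weight advice form part of the outcome, covariates measuring weight and lifestyle are partly being related to themselves.

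**Working it through.** The plan gives no figure on this point to reproduce, so the check is mainly a reading of the rule.

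**1. The rule as printed.** In both tables and both columns the four lifestyle items are joined by *and*. *Or* joins only the drug and lifestyle routes. There is no clause for items that do not apply. Hence:

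bar 5 = in care AND [drugs in past 2 weeks OR (diet or salt AND weight AND smoking AND exercise)]

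**2. Two internal conflicts.** The stem asks about *any* of the listed items, while the list and the definition require all of them. The definition column speaks of *following* advice, the question column of *receiving* it.

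**3. A worked patient.** In care, no drugs; diet yes, exercise yes; no smoking or weight advice reported because neither applies. Score: 2 of 4. The patient is not in bar 5, cannot enter bar 6, and appears as leakage.

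**4. What carries into bar 6.** Take reported drug use to mean the same in bars 1 and 5.
- *T2D:* a drug-free patient enters bar 1 only with FBG ≥126 mg/dl and HbA1c ≥6.5%. Control is HbA1c <8%. Only those from 6.5% to <8% can be wrongly lost at bar 6.
- *HT:* a drug-free patient enters bar 1 only with systolic ≥140 or diastolic ≥90 mmHg. Control needs <140 and <90 on the same mean of the second and third readings. No such patient can be controlled, so bar 6 does not change whatever bar 5 says.

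**5. The regression.** Under *receiving*, smokers and overweight patients are the ones likely to be given the two conditional items, which pushes them towards in treatment. Under *following*, a current smoker is arguably not following the advice, and someone who quit on advice is now a non-smoker; the push may reverse. An artificial association is possible; its sign is not fixed by the text.

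**6. Size, T2D bar 5.** All five inputs are assumptions; none is in the documents.
- C, share of T2D patients in care: 0.30 to 0.50
- d, share of those without drugs: 0.05 to 0.20
- a, share of the drug-free group credited under a relaxed rule: 0.80
- s, smokers: 0.10 to 0.40; o, overweight: 0.20 to 0.50; taken as independent

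It is further assumed that patients report only advice that applies to them.

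Relaxed rule: C[(1−d) + d·a]. All-four rule: C[(1−d) + d·a·s·o]. Difference: C·d·a·(1 − s·o).

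| C | d | s | o | s·o | All four | Relaxed | Difference |
|---|---|---|---|---|---|---|---|
| 0.30 | 0.05 | 0.40 | 0.50 | 0.20 | 28.7% | 29.7% | 0.012 × 0.80 = 1.0 point |
| 0.50 | 0.10 | 0.20 | 0.30 | 0.06 | 45.2% | 49.0% | 0.040 × 0.94 = 3.8 points |
| 0.50 | 0.20 | 0.10 | 0.20 | 0.02 | 40.2% | 48.0% | 0.080 × 0.98 = 7.8 points |

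On these inputs both conditional items apply to only 2% to 20% of drug-free patients. The difference is proportional to a, so a stricter replacement rule gives a smaller shift.

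In planned numbers: 24 × 44 × 5 = 5280 people; at the protocol's 10% prevalence, 528 with T2D. Then 528 × 0.0096 ≈ 5 and 528 × 0.0784 ≈ 41 patients, about 1 to 8 of the roughly 106 per operational district.

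**The case against.** The best defence is that the stem asks about any of the items, so the *and* list may merely enumerate the questions extracted. The questionnaire (Multimedia Appendix 2) is not shown and may hold codes for items that do not apply. This is a fair reason to think the authors may not have meant an all-four rule. It does not cure the text: the definition column sets the classification and is itself conjunctive, and the section says the cascade variables are those in Tables 2 and 3. At best the stem and the rule contradict each other.

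Several stronger readings are tempting, and the objection to each stands:

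- *Non-smokers and normal-weight patients can never count.* The items are self-reported advice, not clinical indication. Someone given blanket advice, someone who quit on advice, or someone who reached normal weight on advice can satisfy them.
- *Control is understated in both cascades.* Not for HT, and for T2D only in the HbA1c band in step 4 of the working.
- *The regression will show smokers and overweight patients as better treated.* That follows only from the *receiving* reading. The lifestyle covariate is defined in Multimedia Appendix 6, which is not shown, so its overlap with smoking is likely rather than proven.
- *The error differs by sex and by district.* It would if smoking, overweight or drug-free management differ, but the article gives no such data.

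Patients on drugs are unaffected, which limits the effect to the drug-free share.

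**Conclusion.** The point holds in this limited form. The printed rule for the non-drug route into bar 5 demands all four items in both tables, excuses none that do not apply, and is at odds with its own question stem and between its two columns. Applied literally, it counts some drug-free in-care patients as leakage when their applicable advice is complete. It can also build an association between the in-treatment outcome and weight or lifestyle, of undetermined direction.

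The size cannot be fixed from the documents. The range of roughly 1 to 8 percentage points of all T2D patients rests wholly on the assumed in-care, drug-free, smoking and overweight shares, on independence of the last two, and on patients reporting only applicable advice; blanket advice would shrink it. No figure is offered for HT. That bar 6 for HT is untouched rests on drug use meaning the same in bars 1 and 5; bar 1 states no recall period, so the tables should make this explicit. Since this is a stated rule for a main cascade bar, it should be corrected before analysis.

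**What to change.** In bar 5 of Tables 2 and 3, before the data are analyzed:

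1. Reconcile the stem with the definition and question columns, so that one rule is stated.
2. Replace the all-four rule with one that does not fail a patient on an item that does not apply. One option is all applicable items, using smoking status and measured BMI to decide whether the smoking and weight items apply, with the BMI cut-off named. An any-item rule would match the stem and is simpler; either is workable if fixed in advance.
3. Use one verb, receiving or following, throughout. If it is following, applicability cannot rest on current smoking or current BMI alone: a person who quit or lost weight on advice should count as having met that item.
4. Show the drug and lifestyle routes separately within bar 5.
5. Keep the all-four rule as a sensitivity analysis only.
6. When reporting the in-treatment model, note where BMI and lifestyle overlap with the outcome definition.

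The cost is a line in each table and a recode. Weight and height are measured and behavioral measures are in the individual questionnaire, so no new data should be needed, provided smoking status is among those measures. The downside is that bar 5 becomes slightly less simple to describe. The change concerns how survey answers are classified and sets no clinical rule.
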